## Abstract

**Background:**

Healthcare workers need to be at work 24 h a day to ensure continuity of care in hospitals. However, shift work - particularly night shifts - can have negative acute and long-term effects on health and productivity due to disturbances in the circadian rhythm. Shift work is also associated with unhealthy lifestyle behaviors such as poor sleep hygiene and diet. The PerfectFit@Night intervention aims to improve sleep and recovery, and reduce fatigue, and therewith contribute to sustainable employability of healthcare workers. The current study describes the intervention and the evaluation and implementation.

**Methods:**

The study population will consist of healthcare workers, nurses and physicians, with night shifts in a large Dutch academic hospital. The intervention consists of individual and environmental intervention elements: i) an e-learning for healthcare workers to increase knowledge and awareness on a healthy lifestyle during night shifts, ii) a powernap bed to take powernaps during night shifts, iii) the availability of healthy food at the department during night shifts, iv) a workshop on healthy rostering at the level of the department, and v) individual sleep coaching among the high risk group. In a longitudinal prospective study, data will be collected 1 month before the start of the intervention, in the week before the start of the intervention, and three and 6 months after the start of the intervention. The primary outcomes are sleep, fatigue, and need for recovery. The implementation process will be evaluated using the framework of Steckler and Linnan. Cost-benefit analyses from the employers perspective will be conducted to understand the possible financial consequences or benefits of the implementation of PerfectFit@Night.

**Discussion:**

The feasibility and effectiveness of this workplace health promotion program will be investigated by means of an effect, process and economic evaluation. If proven effective, PerfectFit@Night can be implemented on a larger scale within the healthcare sector.

**Trial registration:**

Netherlands Trial Register trial number NL9224. Registered 17 January 2021.

## Background

To ensure continuity of care in hospitals, healthcare workers need to be at work 24 h a day. Consequently, the healthcare sector has one of the highest proportions of night workers. In the Netherlands, one out of five workers in the healthcare sector works night shifts [1]. However, studies show that shift work, particularly night shifts, can have a negative effect on the health and productivity of workers, which is mostly due to disturbances in the circadian rhythm and a lack of sleep [2, 3]. Night work could lead to acute problems such as digestive problems, fatigue, loss of sleep [4], and a higher susceptibility to respiratory infections [5], but also to long-term problems, such as chronic stress and chronic sleep loss [6], and lifestyle-related diseases such as diabetes type 2 [7], cardiovascular diseases [8], mental health problems [9, 10], and all-cause mortality [11].

Shift work is also associated with unhealthy behaviors, such as poor sleep hygiene [12], and changes in timing, quantity, and quality of food intake [13]. Unhealthy behaviors are risk factors for several health problems related to shift work, such as diabetes type 2 [14] and cardiovascular diseases [15, 16]. According to the World Health organization (WHO), preventing or delaying these diseases include targeting lifestyle behavior [15].

Because of the high proportion of healthcare workers with night work, interventions specifically aimed at this group of workers are needed. Especially since it is not possible to avoid night shifts in the healthcare sector. Recent reviews of health promotion interventions among night workers conclude that the effectiveness of these interventions is inconclusive and based on heterogeneous interventions, with some interventions showing modest positive effects [17–21]. The interventions that were assessed in these reviews concern a variety of exposures to bright light, policies and timing schedules regarding napping, types and schedules of physical exercise, and healthy meal offers. Besides the differences between studies assessed in these reviews, a moderate positive health and performance effect was found for napping during night shifts [18, 19].

To contribute to an improvement of health and sustainable employability among night workers in the healthcare sector, the PerfectFit@Night intervention is developed to improve sleep and recovery, and to reduce fatigue. We will evaluate the effectiveness of the intervention on sleep, fatigue, and recovery, as well as the implementation. The current paper describes the PerfectFit@Night intervention and the design of the effect, process, and economic evaluation.

## Methods

The PerfectFit@Night intervention is developed by a needs assessment combining existing literature with a participatory approach to ensure that individuals’ needs and preferences, such as individual characteristics (sleep, dietary behavior, personal factors) and the social and physical context (work-private life, roster, work environment), are also taken into account.

Based on the needs assessment, the following program objectives emerged: i) to increase the knowledge and awareness on working healthy during night shifts, ii) to accept taking powernaps and actually take powernaps during night shifts, iii) to have insight in and availability of healthy food/snacks during night shifts, iv) to have knowledge on healthy rostering, and, additionally, v) to provide sleep coaching for night workers with existing sleep problems and fatigue.

### Intervention elements

Based on the needs assessment and program objectives, the intervention consists of the following individual and environmental elements (see Fig. 1): i) an e-learning for night workers to increase knowledge and awareness on a healthy lifestyle during night shifts, ii) a powernap bed to take powernaps during night shifts, iii) the availability of healthy food/snacks at the department during night shifts, iv) a workshop on healthy rostering at the level of the department (for roster makers), and v) individual sleep coaching among the high risk group.

**Fig. 1 Fig1:**
[figure not shown]
Intervention elements of the PerfectFit@Night intervention divided into individual and environmental elements

PerfectFit@Night consists of individual and environmental intervention elements (see Fig. 1). This section describes the intervention elements and the behavioral and environmental components using a behavior change model. For the individual intervention elements, the attitude, social influence, and self-efficacy (ASE) model [22] is used, and for the environmental elements the Analysis Grid for Environments Linked to Obesity (ANGELO) framework [23] is used. The ASE model assumes the need to have the intention to behave a certain way [22]. Attitude, social influence (subjective norms), and self-efficacy influence this intention. The ANGELO framework can be used to describe environmental factors that influence behavior. These factors are divided into physical, economic, political, and sociocultural factors [23].

#### E-learning for night workers

To increase knowledge and awareness on working healthy during night shifts, an interactive e-learning is developed for healthcare workers with night shifts. This e-learning focuses on the effects and possible risks of night work, and it proposes additional information and advice on how to decrease these risks. The e-learning consists of three short modules of approximately ten to fifteen minutes each, of which each on a specific topic, namely the impact of night work on health, sleep and powernaps, and nutrition and physical activity. The e-learning concludes with a test for self-assessment. The night workers receive credits (Continuing Medical Education) to motivate them to start and complete the e-learning.

In line with the ASE model, the e-learning targets i) beliefs about, for example, the working mechanisms of powernaps to change attitude, ii) requirements in the social setting (e.g., subjective norms, social support, role models) to change social influence, and iii) challenging night workers to set goals and experiment to enhance self-efficacy.

#### Powernaps

In order to accept and encourage healthcare workers to take a nap during night shifts, powernap beds were purchased. Following the ANGELO framework, installing a powernap bed at the department, which is placed in a quiet and suitable room (i.e., physical factor), is paid by the participating departments or hospital (i.e., economic factor), and it is allowed by the management to take a powernap (i.e., political and cultural factor). At the individual level, sociocultural factors are role models, social support from colleagues and the management, and social norms regarding powernaps. It is known that attitude towards and acceptance of taking naps during night shifts is challenging. Therefore, the e-learning provides information about the working mechanisms of powernaps and encourages the intention to use powernaps. Besides, examples of good practices in other departments and hospitals are given, and workers of the department are involved as ambassadors (role models).

#### Availability of healthy nutrition at work

To encourage healthy nutrition, healthcare workers with night shifts should have insight in healthy nutrition, and healthy food needs to be offered by the employer. The night workers are informed about the best timing to consume specific nutritional elements through the e-learning module, but also by flyers and a webinar. This information is established in a collaboration with a dietician who specializes in chrono nutrition, based on the latest insights from research and experiences. Following the ANGELO-framework, healthy food is made available during night shifts by providing products (i.e., physical factor) that is paid by the department (i.e., financial factor). The heads of the departments agreed to provide and pay for the food (i.e., political factor). At the individual level, sociocultural factors that are a condition for change in diet to occur are role models (ambassadors), social support from colleagues and the management, and social norms.

#### Workshop on healthy rostering

Having insight in healthy rostering at the level of the department is targeted by a workshop that focuses mainly on staff members, team leaders, and managers dealing with the rosters. The workshop will be tailored to the department. Even though research shows that forward rotating rosters have the best effects, the optimal roster for shift workers remains unknown. The workshop aims to motivate roster makers to have conversations with their workers about the rosters. In line with the ANGELO-framework, the workshop aims to start a conversation at the workplace about changing the rosters (i.e., political factor), and motivate to actually make changes to the rosters (i.e., physical factor). Also important is the acceptance from the management and the workers that the rosters change (i.e., socio-cultural factor), and a sufficient amount of workers to change the rosters (i.e., financial factor). The social context with financial and human resources consequences will also be addressed.

#### Coaching among risk group with existing large sleep problems

The previously described intervention elements are mainly focused on universal prevention of risks due to night work. Additionally, night workers with existing large sleep problems and fatigue are offered sessions with a sleep coach to reduce these problems (indicated prevention). Night workers that score low on subjective global sleep quality (assessed using Pittsburgh Sleep Quality Index (PSQI) [24]) and high on fatigue (assessed using the Short Fatigue Questionnaire (SFQ) [25]) at the baseline measurement are offered coaching sessions, online or face-to-face. The coaches provide evidence-based methods, based on cognitive behavioral therapy insomnia (CGTi), to target the individual problems of the night workers. Participants who accept the invitation for coaching sessions are offered 2–3 sessions of 30–40 min, based on the needs of the individual. During these sessions, the coach proposes the relevant topics to be discussed based on the individual needs and issues of the participant. Before the first session, participants are asked to fill out a screening form, a questionnaire regarding cognitions about sleep, and an online sleep journal for 2 weeks. During the first session, the trajectory and goals are discussed and specified. Then, the participants’ biological rhythm is discussed, specifically taking into account the irregular work shifts. Targeted information and tips about the irregular rhythm and sleep in general are also given by the coach. During the second session, the previous exercises are discussed. Thereafter, practical tips regarding lifestyle, sleeping behavior, and relaxation are given. It is also evaluated whether a third session is needed. During the third session, exercises that need follow-up are discussed, as well as applications of the techniques in the future.

The intervention will be implemented throughout a period of 3 months, and thereafter may continue at the discretion of participating individuals and departments within the hospital.

#### Study design

A prospective study design is used to investigate the effect of the PerfectFit@Night intervention on sleep, fatigue, and recovery. The intervention is implemented at different hospital departments, making randomization at individual level not possible. Randomization at the work department was not possible, because whether and when the interested departments start PerfectFit@Night is highly dependent on the developments regarding the COVID-19 pandemic. Since randomization at individual level nor work department is possible, the intervention is implemented across at least six departments over a 3 months period, whereby departments move from the control condition to the intervention condition. In this phased pre-post approach within each department there are two periods of data collection before the start of the intervention (1 month and right before the start of the intervention) and two periods of data collection thereafter (3 months and 6 months after the start of the intervention).

The study has been approved by the Medical Ethical Review Committee of the Erasmus University Medical Center (Erasmus MC) and registered in the Netherlands Trial Register under trial number NL9224.

### Study population

The study population consists of all healthcare workers working night shifts from at least six different departments of the Erasmus University Medical Center in the Netherlands. The participants that completed the baseline questionnaires were asked to fill out a short questionnaire before the start of the intervention period, and follow-up questionnaires after three and six months after the start of the intervention (i.e., a total of four measurements).

### Sample size

A power calculation was conducted to determine the sample size. The calculation is based on the number of night workers needed to identify a medium effect-size (at least 0.27) in sleep quality, as measured with the Bergen Shift Work Sleep Questionnaire (BSWSQ) [26]. A previous study among nurses working night shifts reported a mean sleep quality of 1.75 with a standard deviation (SD) of 1.26 [26]. The design of the study is a before-after study with four measurements (two before and two after the intervention period). Assuming equal within- and between-person variance with an ICC of 0.05 for clustering at the department level, and an average cluster size of 20, five departments should be included to obtain a power of 0.80 at a significance level of 0.05. This means 100 participants should be included in total. Taking into account an initial participation of 70% and a loss-to-follow-up of 30%, the number of night workers needed at baseline is 204. It could be in practice that cluster sizes are larger than described in this power calculation. This will not have any consequences as we applied the most conservative sample size within this prospective study design with repeated measurements.

### Outcome measures

The outcomes are assessed using a questionnaire which is sent to the night workers of the participating departments both digitally and on paper.

#### Primary outcomes

The primary outcome measures are sleep, fatigue, and need for recovery, which are measured at all four time points.

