### Effect evaluation

Baseline characteristics of the participants and of the departments will be summarized using descriptive statistics to detect possible selection bias and lack of balance between departments. To evaluate the effectiveness of the intervention, linear mixed effects models will be applied for scale-scores, and generalized linear mixed models for dichotomous outcomes. These statistical methods take into account the repeated measures of the study design. The analyses will be adjusted for important confounders based on the individual participants and the department, and both statistical tests and confidence intervals will be calculated (with a significance level of 5%). The difference in starting point across the departments and the multilevel structure of the departments will be taken into account. In order to analyze whether the (in)effectiveness of the intervention is moderated by the implementation factors, the linear and generalized mixed models will be expanded with the process factors that emerge from the process evaluation to evaluate whether higher uptake and quality of implementation is associated with higher effect size.

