### Economic evaluation

To help employers and managers to understand the possible financial consequences or benefits of the implementation of PerfectFit@Night, cost-benefit analyses from the employers perspective will be conducted if the intervention has been proven effective. To perform the economic analysis, three measures are included in the study.

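### Three unranked primary outcomes share one 5% level and one effectiveness verdict with no stated rule, while the sample size fits a single sleep outcome only

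*Protocol article*

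**What the plan says.** All references are to the protocol article.

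- **Primary outcomes:** "The primary outcome measures are sleep, fatigue, and need for recovery, which are measured at all four time points". The Abstract (Methods) gives the same three, also without ranking.
- **Effect evaluation:** mixed models are planned, and "both statistical tests and confidence intervals will be calculated (with a significance level of 5" per cent). No order or division of that level among the outcomes is given.
- **Sample size:** the calculation aims to "identify a medium effect-size (at least 0.27) in sleep quality, as measured with the Bergen Shift Work Sleep Questionnaire (BSWSQ"). The source study "reported a mean sleep quality of 1.75 with a standard deviation (SD) of 1.26". The result is that "five departments should be included to obtain a power of 0.80 at a significance level of 0.05". Fatigue and need for recovery do not enter the calculation.
- **Sleep (under Primary outcomes):** the BSWSQ gives a global score for each shift type, classed as unfavourable or not, and is supplemented with items from the Pittsburgh Sleep Quality Index (PSQI). No single score is named as the primary one.
- **Economic evaluation:** the cost-benefit analyses "will be conducted if the intervention has been proven effective".
- **Abstract (Discussion):** "If proven effective, PerfectFit@Night can be implemented on a larger scale within the healthcare sector".

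**The concern.** Three outcomes have equal standing, yet the plan leads to one yes-or-no verdict. Nothing says whether that verdict needs one outcome, a particular outcome, or all three. The operating characteristics differ sharply between these rules, and the two figures that the article states (5% and 0.80) belong to a fourth thing: a single test of a single sleep score.

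At stake is what a positive verdict means. Under a lenient rule it can rest on the most favourable of three results, and its error rate is not the stated 5%. Under a strict rule the study is less likely to succeed than the stated 0.80 suggests. With the rule left open, it could be settled after the results are seen.

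**Working it through.** **1. Inputs**

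- From Sample size: effect 0.27 (read as SD units), alpha 0.05, power 0.80, equal within- and between-person variance (within-person correlation 0.5), two measurements before and two after, department ICC 0.05, cluster size 20, 100 participants, 70% participation, 30% loss, 204 at baseline.
- From Primary outcomes: three outcomes.
- Assumed, because the article does not give them: two-sided tests, and a common correlation between the three test statistics, varied from 0 to 0.9.

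**2. Reproducing the plan's own sample size**

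- Variance of the change (mean of two after minus mean of two before), in SD² units: 2 × (1 − 0.5)/2 = 0.5.
- Unclustered n = (1.960 + 0.842)² × 0.5 / 0.27² = 53.8.
- Design effect = 1 + 19 × 0.05 = 1.95, so n = 53.8 × 1.95 = 105.0.
- Power at 100 = Φ(0.27/√(0.5 × 1.95/100) − 1.960) = 0.78.
- Inflation: 100/(0.7 × 0.7) = 204.1.

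This is close to the stated 100, 0.80 and 204. Reading 0.27 as raw units with SD 1.26 would give 167 instead. The stated figures therefore fit one outcome tested at the full 0.05.

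**3. Rule A: any one of three suffices**

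With no effect on any outcome and independent tests, the two-sided error is 1 − 0.95³ = 14.3%. Significant results in the favourable direction only give 1 − 0.975³ = 7.3%. For correlated tests, equicorrelated normal statistics were simulated (2 million draws each):

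| Assumed correlation | Any of three, either direction | False benefit only |
|---|---|---|
| 0 | 14.3% | 7.3% |
| 0.3 | 13.6% | 6.8% |
| 0.5 | 12.5% | 6.3% |
| 0.7 | 10.9% | 5.5% |
| 0.8 | 9.8% | 4.9% |
| 0.9 | 8.3% | 4.2% |
| One test, for comparison | 5.0% | 2.5% |

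**4. Rule B: all three must succeed**

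The error is at most 5%. If each outcome had 80% power and they were independent, joint power would be 0.8³ = 0.512. Positive correlation raises this towards, but not above, 0.80. The article gives no power for fatigue or need for recovery, so the 80% for those two is an assumption.

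**5. Rule C: the sized sleep score alone decides**

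Error is 5% and power is as stated. This is the only one of the three rules under which both published figures hold, and the Primary outcomes section does not state it.

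**6. Cost of splitting alpha**

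If each outcome is tested at 0.05/3 = 0.0167, independent tests have a familywise error of 1 − (1 − 0.0167)³ = 4.9%. An outcome with 80% power at 0.05 then has Φ(1.960 + 0.842 − 2.394) = 66%. Restoring 80% multiplies n by (2.394 + 0.842)²/(1.960 + 0.842)² = 1.33. That is about 133 evaluable and 133.4/0.49 = 272 approached.

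**The case against.** The strongest reply is that this is a journal article. A multiplicity rule, a success criterion and the choice of score are commonly left to a full protocol or analysis plan, which is not shown here. That is fair, and the absence of a multiplicity adjustment is not the point made. What stands is that the parts the article does fix (three equal primaries, a one-outcome sample size at full alpha, one verdict) do not fit together unless sleep alone decides. Sizing a study on one of several primaries is not in itself an error.

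Several stronger readings are tempting and are not supported:

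- **That the false-claim rate is 11–14%.** This needs an any-of-three rule, which the text neither states nor excludes, and a correlation of about 0.7 or less, which it does not give. It also counts significant worsening, which nobody would call effective.
- **That each outcome will be tested at an unadjusted 5%.** Effect evaluation names a 5% level and does not say how it is applied across outcomes.
- **That the error reaches 26%.** Six independent tests would give 26.5% (20.8% at correlation 0.5), but the article does not state how many shift-type scores will be tested or that each would count as proof. It supports only the direction: more scores, more error.
- **That the verdict drives roll-out.** The Abstract sentence says only that wider implementation is possible. The condition on the cost-benefit analysis appears in Economic evaluation alone. The Abstract, Discussion and Conclusion describe that analysis without it.

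**Conclusion.** The point holds as a defect in the success rule, not as a fixed error rate. If any one of three outcomes suffices, two-sided familywise error is about 8–14% for assumed correlations from 0.9 to 0. False benefit is about 5.5–7.3% for correlations from 0.7 to 0 (4.2% at 0.9), against 2.5% for one test, and more if several sleep scores count. If all three are required, error is controlled but joint power is about 51% with 80% on each and independence, so the stated 0.80 does not describe the study. The results rest on two-sided tests, no true effect on any outcome (for the error rates), and 80% power on the two outcomes that were not sized (for joint power). The practical consequence named most firmly in the text is the trigger for the cost-benefit analysis.

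**What to change.** State that the effectiveness verdict rests on the one outcome the study is sized for, tested at 5%. This means naming a single BSWSQ score (shift type and scale) that matches the mean of 1.75 and SD of 1.26. Sample size does not identify that score: it speaks of sleep quality, whereas the Sleep section describes a dichotomous global score per shift type and says the BSWSQ lacks a rating of subjective global sleep quality. Then test fatigue, and after it need for recovery, in fixed sequence at 5%. Also say in one place whether the cost-benefit analysis is conditional.

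This takes a few sentences before analysis and costs sleep no power. The small downside is that fatigue and need for recovery can support a confirmatory claim only if sleep succeeds.

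If all three are to remain co-primary, use Holm or Bonferroni with one named score each, and restate power: about 66% at 0.0167 for an outcome with 80% at 0.05. Holm does no worse than this, since only its first step uses 0.0167. Restoring 80% at that level needs about 133 evaluable and 272 approached, instead of 100 and 204.
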